10.3.2. Secondary Outcome Measures

10.3.2.1.WURSS-21-K Symptom Score

- This score is calculated by summing the scores of the 10 questions in the WURSS-21-K that evaluate symptoms.
- Daily diary containing the WURSS-21-K will be distributed at Visit 2, and subjects will be instructed to complete it daily. It will be collected at Visit 3.

10.3.2.2.WURSS-21-K Quality of Life Score

- This score is calculated by summing the scores of the 9 questions in the WURSS-21-K that evaluate quality of life.
- Daily diary containing the WURSS-21-K will be distributed at Visit 2, and subjects will be instructed to complete it daily. It will be collected at Visit 3.

10.3.2.3.Nasal Congestion Severity Score

WURSS-21-K 상기도 감염 설문 - 21 일과 증상 기록

날짜(연월일):  
년 월 일

시간:  
오전 : 오후

병호:

다음 각각의 항목에 대하여 동그라미안에 체크하세요:

|                    | 아프지
않다
0        | 아주
조금
1         | 조금
2 3             | 보통
4 5             | 매우
6 7             |
|--------------------|-----------------------|-----------------------|-----------------------|-----------------------|-----------------------|
| 오늘 얼마나 아프다고 느끼십니까? |  |  |  |  |  |

각각의 증상에 대해 지난 24시간 동안의 감기증상으로 힘들었던 정도를 평가해주세요:

|               | 이러한 증상
은 없었습니다
0 | 아주
조금
1         | 조금
2 3             | 보통
4 5             | 매우
6 7             |
|---------------|------------------------|-----------------------|-----------------------|-----------------------|-----------------------|
| 콧물            |   |  |  |  |  |
| 코막힘           |   |  |  |  |  |
| 재채기           |   |  |  |  |  |
| 목이 아픔         |   |  |  |  |  |
| 목이 간질거리는 느낌   |   |  |  |  |  |
| 기침            |   |  |  |  |  |
| 천음소리          |   |  |  |  |  |
| 머리가 맑지 않고 묵적함 |   |  |  |  |  |
| 가슴이 답답함       |   |  |  |  |  |
| 피로감           |   |  |  |  |  |

지난 24시간 동안, 감기가 당신의 삶의 질에 어떠한 영향을 미쳤나요?

|                         | 전혀
없었습니다
0      | 아주
조금
1         | 조금
2 3             | 보통
4 5             | 매우
6 7             |
|-------------------------|-----------------------|-----------------------|-----------------------|-----------------------|-----------------------|
| 명확하게 생각하는데 지장을 주었다      |  |  |  |  |  |
| 잠을 잘 자는데 지장을 주었다        |  |  |  |  |  |
| 쉽게 숨을 쉬는데 지장을 주었다       |  |  |  |  |  |
| 걸기, 계단 오르기, 운동에 지장을 주었다 |  |  |  |  |  |
| 일상적인 활동에 지장을 주었다        |  |  |  |  |  |
| 집 밖의 일을 하는데 지장을 주었다     |  |  |  |  |  |
| 직안일을 하는데 지장을 주었다        |  |  |  |  |  |
| 다른 사람들과 어울리는데 지장을 주었다   |  |  |  |  |  |
| 개인적인 생활을 하는데 지장을 주었다    |  |  |  |  |  |

어제와 비교해서, 내 감기가 어떻다고 느껴집니까?

| 아주 많이
좋아졌다         | 어느정도
좋아졌다          | 조금 좋아졌다               | 똑같다                   | 조금 나빠졌다               | 어느정도
나빠졌다          | 아주 많이
나빠졌다         |
|-----------------------|-----------------------|-----------------------|-----------------------|-----------------------|-----------------------|-----------------------|
|  |  |  |  |  |  |  |

- This is a 0-3 point scale for evaluating the severity of nasal congestion symptoms. A score of 0 means no symptoms, while a score of 3 indicates severe symptoms that are difficult to endure and interfere with daily life or sleep.
- To be eligible for this study, subjects must have a nasal congestion symptom score of 2 or higher at screening.
- Daily diary containing the nasal congestion symptom score will be distributed at Visit 2, and subjects will be instructed to self-evaluate daily. It will be collected at Visit 3.

#### **Nasal Congestion Severity Score**

| Score | Criteria                                                                                           |
|-------|----------------------------------------------------------------------------------------------------|
| 0     | No symptom                                                                                         |
| 1     | Symptom clearly present but minimal awareness                                                      |
| 2     | Definite awareness of symptom, which is bothersome but tolerable                                   |
| 3     | Symptom that is hard to tolerate, may cause interference with activities of daily life or sleeping |

#### **10.3.2.4.Nasal Symptom Score VAS**

- The severity of nasal symptoms (rhinorrhea, nasal congestion, sneezing) will be evaluated using a Visual Analogue Scale (VAS). The subject will mark their symptom severity on a scale where 0 represents no symptoms at all and 100 represents the most severe symptoms imaginable.
- Daily diary containing the Nasal Symptom Score VAS will be distributed at Visit 2, and subjects will be instructed to self-evaluate daily. It will be collected at Visit 3.

#### **10.3.2.5.Systemic Symptom Score VAS**

- The severity of systemic symptoms (headache, myalgia, chills) will be evaluated using a Visual Analogue Scale (VAS). The subject will mark their symptom severity on a scale where 0 represents no symptoms at all and 100 represents the most severe symptoms imaginable.
- Daily diary containing the Systemic Symptom Score VAS will be distributed at Visit 2, and subjects will be instructed to self-evaluate daily. It will be collected at Visit 3.

#### **10.3.2.6.Duration of Cold Symptom**

- Subjects will be asked if all cold-related symptoms have resolved. If they respond that the cold is completely gone, the date of resolution will be confirmed to assess the total duration of symptoms.
- Daily diary distributed at Visit 2 will be used to check for daily symptom resolution, and it will be collected at Visit 3.

**10.3.2.7.Recovery from Common Cold**

- At Visit 3, cold recovery will be evaluated based on whether all cold symptoms have improved.

**10.3.2.8.Global Evaluation of Efficacy**

- This is a 0-4 point scale to assess the overall satisfaction with the treatment. The subject will self-evaluate (0=very good, 1=good, 2=average, 3=poor, 4=very poor).
- This will be assessed at Visit 3.

**10.3.2.9.EQ-5D-5L (5-level EuroQol 5-dimensional questionnaire)**

- The EQ-5D-5L is a self-reported questionnaire used to evaluate quality of life. It assesses five dimensions—mobility, self-care, usual activities, pain/discomfort, and anxiety/depression—on a 5-point scale. Additionally, subjects will mark their current health status on a vertical VAS ranging from 0 (worst imaginable health state) to 100 (best imaginable health state).
- This will be assessed at Visits 2 and 3.

**10.4. Safety Assessment**

- 1) Adverse events
- 2) Vital signs
- 3) Laboratory test
  - ✓ Complete blood count: RBC, WBC, Hemoglobin, Hematocrit
  - ✓ Liver function test: AST, ALT, BUN, Creatinine, Glucose (Glucose will be evaluated only at Visit 1)

**10.5. Exploratory outcome measures****10.5.1. Questionnaire for Common Cold Pattern Identification**

- To examine the difference in effects by pattern identification, it will be used to classify subjects' patterns.
- It classifies pattern types into 8 categories: Wind-Cold type, Wind-Heat type, Dampness type, Summer-Heat type, Qi deficiency type, Blood deficiency type, Yin deficiency type, and Yang deficiency type. In this study, the six pattern types other than Wind-Cold and Wind-Heat types will be classified as 'Other' to create a total of three pattern types (Wind-Cold type, Wind-Heat type, and Others).
- This will be assessed at Visit 1.

## 10.6. Adverse Events and Serious Adverse Events

### 10.6.1. Definition of Adverse Events

Adverse Event (AE) is any untoward and unintended sign (including abnormal laboratory findings), symptom, or disease that occurs in a subject administered an investigational product, and it does not necessarily have a causal relationship with the investigational product.

#### <Adverse Event Assessment>

Adverse events will be carefully monitored from the time the investigational product is administered. They will be confirmed during subsequent visits through interviews and medical consultations with the investigator. Detailed information will be recorded, including the onset and resolution dates of the adverse event, its severity, outcome, any actions taken in relation to the investigational product, causality with the investigational product, the name of any other suspect medications, and whether and how the adverse event was treated. In the event of an adverse event, subjects must be educated to report it immediately to the investigator and to visit the clinic for treatment. The investigator's contact information must be provided to the subjects. Detailed assessment, recording, and management of adverse events will follow the procedures in Section 10.6.3.

Adverse Drug Reaction (ADR) is any noxious and unintended response to an investigational product at any dose, where a causal relationship with the investigational product cannot be ruled out.

Unexpected ADR is an adverse drug reaction that differs in nature or severity from the information available in the Investigator's Brochure or other relevant drug information.

### 10.6.2. Definition of Serious Adverse Events

Serious Adverse Event / Adverse Drug Reaction (Serious AE/ADR) is an adverse event or adverse drug reaction occurring at any dose of an investigational product that leads to any of the following outcomes

- Death or life-threatening situation.
- Requires or prolongs hospitalization.
- Results in persistent or significant disability/incapacity.
- Causes a congenital anomaly or birth defect in an offspring.
- Other medically significant events, such as drug dependency or abuse, or hematological disorders, that are not listed above.

However, the following are not considered Serious AEs/ADRs

- Hospitalization for a simple observation or examination with no treatment.
- Subject's elective surgery or a pre-planned surgery for an existing condition.

Suspected Unexpected Serious Adverse Reaction (SUSAR) is any serious, unexpected, and suspected

adverse drug reaction that occurs during the use of an investigational product. It must meet all three of the following criteria

- Suspected adverse drug reaction
- Serious
- Unexpected

### 10.6.3. Classification of Adverse Events

#### 1) Severity of Adverse Events

The severity of an adverse event is classified based on its maximum intensity using the following criteria

|                 |                                                                                                                                                                                       |
|-----------------|---------------------------------------------------------------------------------------------------------------------------------------------------------------------------------------|
| Mild     | The subject barely notices it, and it does not interfere with normal daily life or functioning. It typically does not require treatment.                                              |
| Moderate | The subject experiences discomfort and it interferes with normal daily life or functioning. The subject can continue the study, but treatment may be required.                        |
| Severe   | The subject is very uncomfortable, daily life and functioning are impossible, and continued participation in the study is not feasible. Treatment or hospitalization may be required. |

#### 2) Causality Assessment of the Investigational Product

When an adverse event occurs, the investigator will assess its causal relationship with the investigational product based on the following criteria and provide their opinion if necessary.

A causal relationship with an investigational product cannot be statistically tested, so it is determined by considering individual circumstances, medical plausibility (physiological, pathological, pharmacological), and literature. Considering the temporal relationship is also helpful. Additionally, the investigator will consider whether the event disappeared upon discontinuation and reappeared upon re-administration of the drug, as well as any concomitant therapies or medications.

The certainty of the relationship between the adverse event and the investigational product (or other causes, such as underlying disease progression or concomitant treatment) is determined by how well the adverse event can be explained in terms of the following

- ① Known pharmacological actions of the investigational product.
- ② Similar actions previously observed with the investigational product or a drug of the same class.
- ③ Reactions frequently reported in relation to similar drugs.
- ④ A reaction that is temporally related to drug administration (disappears upon drug

discontinuation and reappears upon re-administration).

**<Criteria for Causality Assessment with the Investigational Product>**

|                               |                                                                                                                                                                                                                                                                                                                                                                                                                                                                                                                                                                                                                         |
|-------------------------------|-------------------------------------------------------------------------------------------------------------------------------------------------------------------------------------------------------------------------------------------------------------------------------------------------------------------------------------------------------------------------------------------------------------------------------------------------------------------------------------------------------------------------------------------------------------------------------------------------------------------------|
| Definitely related     | 
 
- There is evidence of drug administration, and the temporal relationship between the investigational product and the adverse event is plausible.
 
- The adverse event is most plausibly explained by the investigational product rather than any other reason.
 
- The adverse event disappears when the investigational product is discontinued.
 
- The result of re-challenge (if performed) is positive.
 
- The adverse event shows a pattern consistent with previously known information about the same investigational product.
 
 |
| Probably related       | 
 
- There is evidence of drug administration, and the temporal relationship between the investigational product and the adverse event is plausible.
 
- The adverse event is more plausibly explained by the investigational product than by other causes.
 
- The adverse event disappears when the investigational product is discontinued.
 
                                                                                                                                                                                                             |
| Possibly related       | 
 
- There is evidence of drug administration, and the temporal relationship between the investigational product and the adverse event is plausible.
 
- The adverse event is judged to be attributable to the investigational product at the same level as other possible causes.
 
- The adverse event disappears when the investigational product is discontinued (if performed).
 
                                                                                                                                                                       |
| Probably not related   | 
 
- There is evidence of drug administration, but there is a more plausible cause for the adverse event.
 
- The result of discontinuing the investigational product (if performed) is negative or ambiguous.
 
- The result of re-challenge (if performed) is negative or ambiguous.
 
                                                                                                                                                                                                                                                                     |
| Definitely not related | 
 
- The subject did not receive the investigational product.
 
- The temporal relationship between the investigational product and the adverse event is not plausible.
 
- There is another clear cause for the adverse event.
 
                                                                                                                                                                                                                                                                                                                            |
| Unknown                | 
 
- The information is insufficient or contradictory, and cannot be supplemented or confirmed.
 
- There is insufficient evidence to determine a connection.
 
- The quality of the evidence is poor or the data is inconsistent.
 
                                                                                                                                                                                                                                                                                                                         |

3) Predictable Adverse Events

- A predictable adverse event is any untoward and unintended reaction that occurs during an intervention, for which a causal relationship with the intervention used in the clinical trial cannot be excluded.

① GGTCS

- 1) Pseudoaldosteronism: May present with decreased urine output, swelling of the face and extremities, heavy eyelids, stiff hands, elevated blood pressure, and headache. Since formulations containing 1g or more of Glycyrrhizae Radix et Rhizoma per day may cause pseudoaldosteronism (hypokalemia, increased blood pressure, sodium retention, edema, weight gain) with long-term use, subjects must be closely monitored (by measuring serum potassium levels), and the medication should be discontinued if any abnormalities are found.
- 2) Myopathy: Myopathy may occur as a result of hypokalemia. Subjects should be closely observed, and the medication should be discontinued if abnormalities such as weakness, limb cramps, or paralysis are observed.
- 3) Skin: May cause rash, erythema, itching, etc.
- 4) Gastrointestinal System: May cause loss of appetite, stomach discomfort, nausea, vomiting, diarrhea, etc.
- 5) Autonomic Nervous System: May cause insomnia, excessive sweating, tachycardia, frequent urination, palpitations, systemic weakness, mental agitation, etc.
- 6) Urinary System: May cause micturition disorders.

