 Screening test should be conducted within one day before Visit 2 and the results of clinical laboratory test should be able to be checked at Visit 2.

 CBC (erythrocyte count, leukocyte count, hemoglobin, and hematocrit); LFT (AST, ALT, BUN, creatinine, and glucose).

 If pregnancy status is uncertain, urine hCG test for pregnancy confirmation following will be conducted, and the result must be negative.

|                                                               |                               |   |   |   |
|---------------------------------------------------------------|-------------------------------|---|---|---|
|                                                               | Global Evaluation of Efficacy |   |   | X |
|                                                               | EQ-5D-5L                      |   | X | X |
| Prescription and Delivery of Assigned Investigational Product |                               |   | X |   |
| Distribution and Instruction for Common Cold Dairy            |                               |   | X |   |
| Compliance Test                                               |                               |   |   | X |
| Common Cold Dairy Check                                       |                               |   |   | X |
| Combined Medication Evaluation                                |                               |   | X | X |
| Dropout Status Check                                          |                               |   | X | X |
| Adverse Reaction Evaluation                                   |                               |   | X | X |
| Instruction for Visit                                         |                               | X | X |   |
| Completion of Trial Check                                     |                               |   |   | X |

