### 5.2. Exclusion Criteria

- 1) Those with sinusitis, allergic rhinitis, pneumonia, influenza, COVID-19, cough or sore throat with sudden fever above 38 °C, bronchitis, otitis media, tonsillitis (if accurate examination is necessary, paranasal sinuses (PNS) view or chest X-ray will be conducted)
- 2) Diagnosis of chronic respiratory disease (chronic obstructive pulmonary disease, bronchial asthma, bronchiectasis, interstitial lung disease, and other chronic respiratory diseases)
- 3) Those who had taken antibiotics, antivirals, steroids, nasal decongestants, antihistamines, antitussives, expectorants, or other medications to alleviate symptoms of the common cold within 1 week of screening
- 4) Liver or renal impairment (ALT, AST, and creatinine  $\geq$  3 times the upper normal limit at screening)
- 5) Those with generic disorders such as galactose intolerance, Lapp lactase deficiency, or glucose-galactose malabsorption
- 6) Pseudo-aldosteronism or myopathy induced by hypokalemia
- 7) Comorbidities that interrupt the treatment of cancers or clinically significant disorders of the kidney, liver, psychiatric system, cardiovascular system, respiratory system, endocrine system, or central nervous system thus interfering with the assessment of efficacy and safety of the investigational drug or completion of the clinical study
- 8) Unregulated hypertension (systolic blood pressure  $\geq$  160 mmHg or diastolic blood pressure  $\geq$  100 mmHg)
- 9) Unregulated diabetes mellitus (fasting blood sugar  $\geq$  180 mg/dL)
- 10) History of hypersensitivity reaction to materials of drugs used in this clinical trial
- 11) History of alcoholism or substance abuse
- 12) Current smokers or those with history of smoking more than 30 packs/year
- 13) Pregnant or lactating women
- 14) Those who do not use medically acceptable contraception (e.g., intrauterine device with proven pregnancy failure rate in spouse or partner, simultaneous use of barrier method for men or

women with spermicide, or surgical procedures, such as vasectomy, tubectomy, tubal ligation, or hysterectomy for oneself or one's partner) during the clinical trial

- 15) Those who participated in other clinical trials within 30 days before participation in this clinical trial
- 16) Those determined by investigators to be ineligible to participate in this trial

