- The subject's height and weight will be measured and recorded via a body composition analysis.
- 7) Laboratory and Pregnancy Test
- The laboratory test items are as follows. For women of childbearing potential, a urine hCG test will be measured after an interview if there is any uncertainty about pregnancy status.
    - ✓ Complete blood count: RBC, WBC, Hemoglobin, Hematocrit, Platelet
    - ✓ Liver function test: AST, ALT, BUN, Creatinine, Glucose
  - The investigator may conduct additional tests related to any abnormal results.
- 8) EKG
- EKG will be performed to check for abnormal findings, and if any are present, the subject will be excluded. EKG results from within 2 weeks prior to obtaining consent are acceptable as screening results (when using test results from another institution, a results sheet that can confirm the findings must be secured.).
  - Investigator may conduct additional tests related to any abnormal results.
- 9) Chest, PNS (paranasal sinuses) X-ray

- Chest or PNS X-ray will be performed if the investigator deems a differential diagnosis necessary.
- Chest X-ray will be checked for findings suggestive of diseases that are part of the exclusion criteria, such as consolidation, atelectasis, emphysema, fibrosis, or a mass.
- PNS X-ray will be checked for findings suggestive of sinusitis, such as mucoperiosteal thickening, haziness, or air-fluid levels in the sinuses.

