#### 12) Confirmation of Inclusion/Exclusion Criteria

- Only for subjects who have voluntarily signed the clinical trial consent form, final confirmation of eligibility based on the inclusion and exclusion criteria will be made at the screening visit using the demographic survey, medical and treatment history (drug history) survey, physical examination, vital signs measurement, laboratory tests, pregnancy test, Chest and PNS X-rays, and EKG. The final decision on suitability will be made by referencing the laboratory test results and recorded. The subject will then be notified by phone to inform them of the clinical trial schedule and precautions, and to set the date for the baseline visit.

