## 2) Confirmation of Adverse Events

- The investigator must record all adverse events that occur during the clinical trial. The investigator will assess the adverse event and record the name of the event, onset date, resolution date, severity, causality, actions taken, and outcome.
- 3) Vital Signs Measurement
- Vital signs including blood pressure (systolic, diastolic), pulse rate, and body temperature will be measured. Blood pressure and pulse rate will be measured using an automated sphygmomanometer while the subject is seated after resting for at least 3 minutes at every visit. Body temperature will be measured using an electronic thermometer after blood pressure is measured.
- 4) Assessments of WURSS-21-K, Nasal Congestion Severity Score, Nasal Symptom Score VAS, Systemic Symptom Score VAS, Global Evaluation of Efficacy, EQ-5D-5L, and duration of cold symptoms.
- 5) Laboratory Test
- Subjects will undergo laboratory tests.
    - ✓ Complete blood count: RBC, WBC, Hemoglobin, Hematocrit
    - ✓ Liver function test: AST, ALT, BUN, Creatinine
  - The investigator may conduct additional tests related to any abnormal results.
- 6) Return of Investigational Products and Compliance Test
- Subjects must return any investigational products remaining from the last 7 days. The pharmacist will check the quantity of returned products, document the medication administration to confirm that each subject took the correct dose, and verify that the investigational product inventory matches the usage records.
- 7) Cold Diary Check
- The cold diary distributed at Visit 2 will be checked to ensure it has been properly completed.

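### Section 10.6.3 requires serum potassium monitoring with a stop rule, but potassium is on no scheduled laboratory panel, at screening or after dosing

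*Protocol*

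**What the plan says.** Section 10.6.3, part 3 (Predictable Adverse Events), GGTCS item 1, describes pseudoaldosteronism as a possible effect of long-term use of formulations with at least 1 g of Glycyrrhizae Radix per day. It draws this instruction from the warning: "subjects must be closely monitored (by measuring serum potassium levels), and the medication should be discontinued if any abnormalities are found". Item 2 adds a separate stop for weakness, limb cramps or paralysis.

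The laboratory tests are listed in five places:

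- Schedule Summary, footnote 2: "CBC (erythrocyte count, leukocyte count, hemoglobin, and hematocrit); LFT (AST, ALT, BUN, creatinine, and glucose".
- Section 10.1, laboratory footnote: the same list.
- Section 10.2.1, item 7 (Visit 1): "Complete blood count: RBC, WBC, Hemoglobin, Hematocrit, Platelet", followed by AST, ALT, BUN, creatinine and glucose.
- Section 10.2.3, item 5 (Visit 3): RBC, WBC, hemoglobin and hematocrit, then "Liver function test: AST, ALT, BUN, Creatinine".
- Section 10.4: the same four blood count items, then "Liver function test: AST, ALT, BUN, Creatinine, Glucose (Glucose will be evaluated only at Visit 1").

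Two entries bear on screening. Exclusion criterion 6 in section 5.2 is "Pseudo-aldosteronism or myopathy induced by hypokalemia". Section 10.2.1, item 12 states that "final confirmation of eligibility based on the inclusion and exclusion criteria will be made at the screening visit", and names laboratory tests among the inputs.

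**The concern.** The instruction is mandatory, names the assay, is addressed to the trial's subjects and carries a treatment decision. A site that works from the visit schedule would never carry it out. Three things follow.

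- No scheduled test would show a low potassium in a subject without symptoms, either before or after dosing.
- If an unscheduled test shows a low value, there is no Visit 1 value to compare it with when causality is judged under 10.6.3.
- The trial sets out to evaluate safety, but would have no systematic data on the laboratory sign of the first reaction it lists as predictable.

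**Working it through.** The protocol gives no figure to reproduce here. The check sets the instruction beside the dose, the panels and the timing.

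**1. Does the warning cover the trial dose?**
- Licorice root per packet: 0.67 g (section 8.1). Packets: 3 per day for at most 7 days, 21 in all (section 9.1).
- Daily dose: 0.67 × 3 = 2.01 g, against the 1 g named in 10.6.3. Ratio: 2.01 / 1 = 2.01.
- Full course: 0.67 × 21 = 14.07 g.

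The daily dose is about twice the level named. The duration is short, which matters for risk and is taken up below.

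**2. Is potassium on any panel?**

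| List | Analytes | Potassium |
|---|---|---|
| Schedule Summary, footnote 2 | 4 blood count + 5 chemistry = 9 | no |
| 10.1, footnote | 4 + 5 = 9 | no |
| 10.2.1, Visit 1 | 5 + 5 = 10 | no |
| 10.2.3, Visit 3 | 4 + 4 = 8 | no |
| 10.4 | 4 + 5 = 9 (glucose at Visit 1 only) | no |

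The lists differ slightly on platelets and glucose, but none contains potassium or any other electrolyte. Scheduled potassium measurements: 0 × 176 = 0.

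**3. Could a scheduled draw trigger the stop?**
- Under section 9.4, dosing starts on the evening of the prescription date: 1 packet on Day 0.
- Days 1 to 6 at 3 per day: 3 × 6 = 18. Taken by the evening of Day 6: 1 + 18 = 19.
- Remaining at the earliest Visit 3 (Day 7), with no missed dose: 21 − 19 = 2, or 2/21 = 10%. On Days 8 to 10: 0.

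Visit 3 is the only scheduled draw after dosing begins, so even a potassium result from that visit comes too late to guide stopping.

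**4. What unscheduled routes exist?**
- Sections 10.2.1 and 10.2.3 allow further tests related to abnormal results.
- Section 10.2.4 allows laboratory tests at an additional visit, at the investigator's discretion.
- Section 10.6.4 calls for a final laboratory test if the study must be ended early because of an adverse event.

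All are optional or reactive, and none names potassium.

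**The case against.** The strongest reply is that the warning is premised on long-term use. This trial doses for at most 7 days and stops sooner if the cold resolves. The sentence gives no time point, frequency or threshold, so it can be read as a general precaution about licorice and not as a visit procedure. Investigators are bound by the whole protocol and can order potassium at an additional visit. Other safeguards exist: blood pressure is taken at every visit, uncontrolled hypertension is excluded, a screening EKG is done, and item 2 stops dosing for muscle symptoms. Only the 88 subjects allocated to GGTCS receive licorice. Exclusion criterion 6 names clinical conditions, which history and examination can address.

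Much of this stands, as limits on the size of the problem:

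- The risk over 7 days is limited, and no event rate is estimated here.
- The test is unscheduled, not impossible.
- Exclusion criterion 6 can be applied without an assay, so it only supports the point. What screening would miss is an undiagnosed low value.
- The number exposed to licorice is 88. The count of 176 is used because a blinded schedule applies to both arms.

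The contradiction remains. Section 10.6.3 knows the course is short and still says subjects must be monitored by this test, with no exemption. Blood pressure, EKG and symptoms do not measure potassium. If the sponsor holds that potassium is unnecessary over 7 days, the mandatory wording is what is wrong. Either way the text needs to change.

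**Conclusion.** The point holds. A mandatory safety instruction with a stop rule has no scheduled measurement behind it: 0 of 5 laboratory lists include potassium, and 0 measurements are scheduled in 176 subjects, at a daily licorice dose twice the level that prompts the warning. The conclusion rests on the protocol's own text; the count of remaining packets also assumes no missed doses. This is a patient-safety and consistency defect that should be corrected. It is not a threat to the trial: no efficacy result, test or sample size changes, and the 7-day limit keeps the clinical risk small.

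**What to change.** 1. Add serum potassium to the existing Visit 1 and Visit 3 draws: section 10.2.1 item 7, section 10.2.3 item 5, section 10.4, and the laboratory footnotes of the Schedule Summary and section 10.1. The Schedule Summary already requires that "the results of clinical laboratory test should be able to be checked at Visit 2", so the screening value would be known before the first dose. It would also serve as the baseline and support exclusion criterion 6.
2. Reword section 10.6.3, GGTCS item 1, along these lines: *Serum potassium will be measured at Visits 1 and 3. During dosing it will be measured at an additional visit (10.2.4) when symptoms or signs suggest pseudoaldosteronism or myopathy, and the medication will be discontinued if it is abnormal.* The sponsor should also state what counts as abnormal. Keep the stop in item 2 as it is.

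The Visit 3 value supplies safety data and is not meant to guide stopping; the symptom-triggered test does that.

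The cost is one assay on blood already drawn at two visits: 2 × 176 = 352 assays, plus one per screening failure and occasional triggered tests. No scheduled visit is added. The analysis text need not change, because section 11.3 already compares values before and after treatment for each laboratory variable.
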